## **7.8 Continuation of intervention after the trial**

Steroid treatment will be given in line with standard clinical practice during the trial. Neither oral nor intratympanic steroid courses are usually repeated, unless a new episode of SSNHL occurs. Once the participant completes or leaves the trial, they will not receive further steroid courses under the direction of the trial team, however they will be able to receive steroid treatment as part of their standard care.

While not part of the clinical trial, clinicians are encouraged to follow their usual local protocols for standard care of participants with ISSNHL in terms of the indication for MRI internal auditory meati to exclude a vestibular schwannoma and referral to audiology for discussion of hearing rehabilitation options.

## **7.9 Intervention supply and storage**

Both oral steroid (Prednisolone) and intratympanic injection steroid (Dexamethasone) will be packaged, stored, prescribed and dispensed as per routine local practice. No trial specific supply, labelling or storage requirements will be needed.

## **7.10 Participant information**

Participants will be provided with information leaflets specific to the intervention(s) they received, detailing precautions following intervention (e.g. keeping the ear dry to avoid infection), possible side effects, and where to seek further information or assistance if needed.

## **7.11 Adherence**

### **7.11.1 Adherence criteria**

A per protocol analysis will be performed for the primary outcome, and for the purposes of this, adherence to the oral steroid group will be defined as receiving prednisolone every day for 7 days, with treatment initiated within 4 weeks of symptom onset and not having the intratympanic treatment.

Adherence to intratympanic treatment group will be defined as receiving 3 intratympanic injections of dexamethasone (either 3.3 mg/ml or 3.8 mg/ml) spaced 7+/- 2 days apart, unless the course of injections was reduced to 1 or 2 injections on the basis of pure tone audiogram confirmed resolution of hearing loss or evidence of further sensorineural hearing loss, as well as not having received any oral steroid (prednisolone) with treatment initiated within 4 weeks of symptom onset. A reduction in course duration for intratympanic injection for any other reason will not be considered per protocol.

Adherence to the combined treatment group will require the criteria above to be met for both interventions. Additionally, if oral treatment is initiated within 4 weeks of symptom onset

---

then intratympanic treatment should be commenced up to four days preceding or following this.

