### 1.2.3 Choice of intervention

Oral steroid (Prednisolone) is included as an intervention as this is recommended in US guidelines (1), and used by most ENT clinicians across the UK (9,14). As the current standard of care, this represents control intervention.

Intratympanic steroid (dexamethasone) is included as a recent survey suggested 62% of UK ENT surgeons use intratympanic steroid injection in the treatment of ISSNHL (9) with dexamethasone the most commonly used steroid. 80% of surgeon's space injections 2-7 days apart (9), leading to the trial recommended schedule.

The third intervention is combined oral and intratympanic steroids, with the first intratympanic injection occurring within a period  $\pm 4$  days of starting oral steroids.

Meta-analysis shows no evidence that one intratympanic steroid regime is superior (10), and so the most commonly used agent (dexamethasone) and frequency of injection (three) in the UK have been adopted. For the one third of ENT surgeons not currently using intratympanic injection for ISSNHL, the technique is easy to learn. The trial team will assist in training surgeons either remotely via videoconferencing and pre-recorded video materials, or on-site if required. This study will help disseminate new skills.

We have not incorporated a placebo arm as it would be unethical to withhold standard care with steroids (2,8), and during participant consultation, participants said they would not accept a placebo.

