## 7 TRIAL INTERVENTION

### 7.1 Trial intervention and dosing schedule

Participants will be randomised to receive:

- Oral steroid (Prednisolone as tablets) 1mg/kg/day up to 60mg/day for 7 days.

OR

- Intratympanic steroid (Dexamethasone) three intratympanic injections 3.3mg/ml or 3.8mg/ml spaced 7±2 days apart (see below for technique).

OR

- Combined oral (Prednisolone) and intratympanic (Dexamethasone) steroid as described above, with the first intratympanic injection occurring within four days of starting oral steroids.

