## 8 OUTCOME MEASURES

### 8.1 Internal Pilot Outcome

The success of the 9-month internal pilot study will be based upon the recruitment rate, adherence to the treatment allocation and dropout rate. At 9 months, it is anticipated that the trial will have recruited 81 participants from at least 36 centres. For the trial to continue pre-defined stop-go criteria must be met. A traffic light system has been designed to determine continuation to the full trial:

**Green:** Recruitment rate  $\geq 100\%$ , adherence rate  $\geq 90\%$ , and dropout rate  $< 5\%$ . If all three criteria are met, the trial will continue with the protocol unchanged.

**Amber:** Recruitment rate 70-99%, adherence rate 70-89%, or dropout rate 5-10%. If one or more of the criteria are met, the trial will be reviewed to determine the changes (if any) that could be made to improve whichever criteria are not at the green level.

**Red:** Recruitment rate  $< 70\%$ , adherence rate  $< 70\%$ , or dropout rate  $> 10\%$ . If one or more of these criteria are met, this will be discussed with the Trial Steering Committee (TSC) and funder regarding feasibility of the trial continuing.

**Table 1:** Internal pilot progression criteria

|                         | Red  | Amber   | Green |
|-------------------------|------|---------|-------|
| Recruitment threshold   | <70% | 70%-99% | ≥100% |
| Adherence threshold     | <70% | 70%-89% | ≥90%  |
| Drop-out rate threshold | >10% | 5-10%   | <5%   |

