#### **Week 1 $\pm 2$ days after first injection**

The following should be performed in the intratympanic injection arm and combination treatment arm:

- Pure tone audiogram (0.5-8.0kHz range)
- 2nd intratympanic injection

NOTE: complete resolution of hearing may allow intratympanic steroid treatment to be terminated after only one treatment

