#### **Week 2 $\pm 2$ days after first injection**

The following should be performed in the intratympanic injection arm and combination treatment arm:

- Pure tone audiogram (0.5-8.0kHz range)
- 3rd intratympanic injection

NOTE: complete resolution of hearing may allow intratympanic steroid treatment to be terminated after only two treatments

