**Table 3: Schedule of Assessments**

| Assessments                                            | Visits    |          |                                               |                                               |                    |                   |                      |
|--------------------------------------------------------|-----------|----------|-----------------------------------------------|-----------------------------------------------|--------------------|-------------------|----------------------|
|                                                        | Screening | Baseline | From first injection                          |                                               | From randomisation |                   |                      |
|                                                        |           |          | 2 nd injection
(week 1 ±2 days) | 3 rd injection
(week 2 ±2 days) | Weekly             | Week 6
±7 days | Week 12
±7 days   |
| Eligibility check                                      | All       |          |                                               |                                               |                    |                   |                      |
| Valid informed consent                                 |           | All      |                                               |                                               |                    |                   |                      |
| Relevant medical history taken                         |           | All      |                                               |                                               |                    |                   |                      |
| Concomitant medication check                           |           | All      |                                               |                                               |                    |                   |                      |
| Demographic information                                |           | All      |                                               |                                               |                    |                   |                      |
| Randomisation                                          |           | All      |                                               |                                               |                    |                   |                      |

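### The adherence definition and the visit schedule count the third injection from different starting points, so a participant who keeps every visit window can be classed as non-adherent in the per-protocol analysis

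*Protocol*

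**What the plan says.** Four places in the protocol set the timing of the injections.

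- **7.1 Trial intervention and dosing schedule** describes the intratympanic course as "three intratympanic injections 3.3mg/ml or 3.8mg/ml spaced 7±2 days apart (see below for technique". The combined arm receives the same course.
- **7.11.1 Adherence criteria** carries this spacing into the definition of adherence: "spaced 7+/- 2 days apart, unless the course of injections was reduced to 1 or 2 injections". A shortened course counts as adherent only when the audiogram shows resolution or further sensorineural loss. The combined arm must meet the criteria for both treatments.
- **Section 9 Trial procedures** places the second injection at week 1 and the third at week 2. Each has a tolerance of two days either way, and both are counted from the first injection.
- **Table 3** repeats those windows under the column heading "From first injection".

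Section 7.11.1 also states what the definition is for: "A per protocol analysis will be performed for the primary outcome, and for the purposes of this, adherence" is then set out arm by arm. Section 14.2 makes intention-to-treat the primary analysis and per-protocol a secondary or sensitivity analysis of the primary outcome.

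**The concern.** A spacing rule is naturally read as applying to each gap between successive injections. The visit schedule applies its tolerance to each visit's distance from the first injection. For the second injection the two are identical. For the third they differ: the schedule's tolerance does not move with the actual date of the second injection, while the spacing rule's does.

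A site can therefore follow Section 9 and Table 3 exactly and produce a participant who fails 7.11.1. It can also follow 7.1 exactly and produce a third visit outside its window. Section 7.11.1 makes no allowance for a participant who was inside the visit windows.

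What is at stake is membership of the per-protocol set. The oral arm has no injection dates, so nobody in it can be removed on this ground. Both key comparisons in 14.2 use oral steroid as the reference, so any such removals fall on one side of each. The exploratory comparison of the two injection arms is exposed on both sides. The documents do not allow the direction of any resulting bias to be stated.

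**Working it through.** The protocol gives no computed figure on this point, so there is none to reproduce. The check enumerates whole-day combinations, with the first injection as day 0.

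**Inputs**

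- Spacing rule (7.1, 7.11.1): each gap is 7 ± 2, so 5 to 9 days.
- Second visit (Section 9, Table 3): 7 ± 2, so day 5 to 9.
- Third visit (Section 9, Table 3): 14 ± 2, so day 12 to 16.

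**Step 1. First gap.** The spacing rule gives day 5 to 9 and the visit window gives day 5 to 9. There is no conflict.

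**Step 2. Visit windows tested against the spacing rule.** Second gap = day of third − day of second. The smallest is 12 − 9 = 3 and the largest is 16 − 5 = 11. All 25 pairs, with breaches of 5 to 9 in bold:

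| Second on day | Third on 12 | 13 | 14 | 15 | 16 |
|---|---|---|---|---|---|
| 5 | 7 | 8 | 9 | **10** | **11** |
| 6 | 6 | 7 | 8 | 9 | **10** |
| 7 | 5 | 6 | 7 | 8 | 9 |
| 8 | **4** | 5 | 6 | 7 | 8 |
| 9 | **3** | **4** | 5 | 6 | 7 |

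Six of 25 pairs keep both visit windows and break the spacing rule; 19 satisfy both.

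**Step 3. Spacing rule tested against the visit window.** Day of third = first gap + second gap. The smallest is 5 + 5 = 10 and the largest is 9 + 9 = 18, against a window of 12 to 16. The pairs of second and third day that fall outside are (5,10), (5,11), (6,11), (8,17), (9,17) and (9,18), again 6 of 25.

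**Step 4. What a breach in Step 2 requires.** Write the second visit as day 7 + a and the third as day 14 + b, with a and b each between −2 and +2. The gap is 7 + b − a, so a breach needs b and a to differ by at least 3. As neither exceeds 2 in size, the two visits must deviate in opposite directions.

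**Step 5. Dependence on booking.** If the third injection is always given 7 days after the second, it falls on day 12 to 16 and every gap is 7, so there is no conflict. If the third is always given on day 14, the gaps run from 14 − 9 = 5 to 14 − 5 = 9, and again there is none. Conflict arises only when the two dates vary with some independence.

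**Step 6. After alignment.** With one anchor used in all places, 0 of the 25 in-window pairs conflict.

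**The case against.** The strongest reply is that this is an edge case. The rules share the first gap and agree on 19 of 25 day pairs, so they are not mutually exclusive and a site can meet both. Every failing in-window pair needs opposite deviations, and two ordinary booking habits produce no conflict at all. The spacing phrase could also be read as shorthand for the weekly schedule that Table 3 spells out. The consequences are limited: the primary analysis is by intention to treat, and the primary outcome is timed from randomisation, so an injection date does not move it.

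Most of this stands and limits the size of the point. The shorthand reading does not dispose of it, because 7.11.1 is the operative definition for the per-protocol analysis and, applied as written, excludes some participants who kept the schedule.

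Three stronger readings are tempting, and the documents do not support them.

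- **A share of participants.** A reader might take 6/25 = 24% as the proportion of injection-arm participants mislabelled, or 10/81 = 12.3% if days are weighted 1:2:3:2:1 around the nominal day. Both assume that the second and third dates vary independently and that all three injections are given. The protocol gives no distribution of visit days, and it permits shorter courses, which have no second gap.
- **A ceiling on pilot adherence.** With two thirds of participants in injection arms, the same assumptions give 1 − (2/3)(0.24) = 0.84, or 1 − (2/3)(0.123) = 0.92, against the green limit of 90% in 8.1. These are expected values under assumed timing, not bounds; full adherence is possible under both rules. Section 8.1 says pilot success "will be based upon the recruitment rate, adherence to the treatment allocation and dropout rate", without citing 7.11.1, so the link to the progression criteria is not established.
- **A third conflicting rule in 1.2.3.** That section says most surveyed surgeons "space injections 2-7 days apart (9), leading to the trial recommended schedule". The range only partly overlaps 5 to 9 days, but it is background on practice and includes 7 days. It is not an operative rule.

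**Conclusion.** The point holds as an internal contradiction of limited reach. Read literally, 7.1 and 7.11.1 conflict with Section 9 and Table 3 on the gap between the second and third injections: 3 to 11 days under the visit windows, 5 to 9 under the spacing rule. Six of 25 day pairs conflict in each direction. A participant can comply with the visit schedule and still be excluded from the per-protocol analysis, and this can happen only in the two injection arms.

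The conclusion rests on reading the spacing as the gap between successive injections and on counting whole days. It does not rest on any assumed frequency. How many participants would be affected cannot be derived from the protocol and may be close to none. The primary estimate is untouched, and no effect on the pilot decision is shown. It is still worth correcting: the per-protocol result is a named sensitivity analysis of the primary outcome, and its membership rule should not contradict the schedule that sites are told to follow.

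**What to change.** Reconcile 7.1, 7.11.1, Section 9 and Table 3 so that they state one timing rule with one anchor, making explicit whether the third injection is counted from the first or from the second. The choice belongs to the clinical team; no timing is proposed here. Score per-protocol membership against that same rule. If the pilot adherence criterion in 8.1 is meant to use the 7.11.1 definition, say so there and score it the same way.

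The cost is protocol wording only. Sample size, outcomes and the primary analysis are unchanged.

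### The combined-arm adherence rule in section 7.11.1 inherits both single-route exclusions, so taken literally no combined-arm participant can be per protocol

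*Protocol*

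**What the plan says.** Section 7.11.1 sets out who counts as adherent, and ties the definitions to one use: "A per protocol analysis will be performed for the primary outcome, and for the purposes of this, adherence to the oral steroid group" is how the passage opens.

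- **Oral arm.** Prednisolone every day for 7 days, "with treatment initiated within 4 weeks of symptom onset and not having the intratympanic treatment".
- **Intratympanic arm.** Three dexamethasone injections at the stated spacing (fewer only for audiogram-confirmed resolution or further loss), "as well as not having received any oral steroid (prednisolone) with treatment initiated within 4 weeks of symptom onset".
- **Combined arm.** "Adherence to the combined treatment group will require the criteria above to be met for both interventions". A further sentence adds that, if oral treatment starts within 4 weeks of onset, "then intratympanic treatment should be commenced up to four days preceding or following this".

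Section 14.2 makes intention-to-treat the basis of all primary analyses and calls the per-protocol analysis secondary or sensitivity, for the primary outcome only. Combination versus oral is one of the two key comparisons.

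Section 8.1 says of the pilot: "The success of the 9-month internal pilot study will be based upon the recruitment rate, adherence to the treatment allocation and dropout rate". Its adherence bands are red below 70%, amber 70–89% and green 90% or more. It does not refer to section 7.11.1.

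**The concern.** Each single-route definition contains a clause excluding the other route. The combined-arm rule takes over the preceding criteria for both interventions and sets neither clause aside. The protocol therefore fixes a rule that contradicts itself for one of three arms, and that arm is one side of a key comparison.

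An analyst who follows the text gets no combined-arm per-protocol set. One who follows the evident intent has to depart from the text, and should not be making that choice once outcome data can be seen.

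Two smaller problems sit beside it. The combined arm inherits a 4-week limit on starting treatment that does not match the closing sentence. The pilot stop-go criterion uses an adherence rate whose definition section 8.1 does not give.

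**Working it through.** **1. The plan's own sample size (section 14.1), to fix the denominators.** Inputs: difference 10 dBHL, SD 25 dBHL, two-sided alpha 0.025, power 90%.

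- Normal approximation: n = 2 × (25/10)² × (2.2414 + 1.2816)² = 12.5 × 12.41 = 155.1, so 156 per arm.
- Noncentral t: power is 0.8992 at 156 and 0.9012 at 157, so 157 per arm, as stated.
- Attrition: 157 / 0.9 = 174.4, so 175 per arm and 525 in total, as stated.

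**2. The combined-arm rule, clause by clause.**

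| Source in 7.11.1 | Oral steroid | Intratympanic steroid |
|---|---|---|
| Oral criteria | full course | must not be given |
| Intratympanic criteria | must not be given | full course |
| Combined arm, literal (both rows apply) | given and not given | given and not given |
| Closing sentence for the combined arm | given | given, within four days either side |

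The third row cannot be satisfied, so the literal per-protocol count is 0 of 175. The fourth row presupposes that both are given, so the intended rule is the course and timing criteria of both routes without the exclusions. On that reading up to 175 of 175 can be adherent.

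**3. The 4-week limit.** Section 4.1 allows randomisation up to four weeks (28 days) after onset. Take a combined-arm participant who starts oral treatment on day 27 and has the first injection on day 30.

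- Closing sentence: oral start within 28 days, and a gap of 30 − 27 = 3 days, within four. Met.
- Inherited intratympanic limit: first injection on day 30, after day 28. Not met, if the limit applies to the injection.

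Whether it does is unclear. In the intratympanic definition the timing phrase follows directly on the excluded oral steroid and could be read with either. Two analysts could classify this participant differently.

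**4. The pilot rate, only if the literal wording were carried into section 8.1.** Inputs: 81 participants expected at 9 months; 1:1:1 allocation (section 6.4.3). With n_c in the combined arm, all scored non-adherent, the ceiling is (81 − n_c)/81.

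| n_c | Ceiling | Band |
|---|---|---|
| 27 | 54/81 = 66.7% | red |
| 25 | 56/81 = 69.1% | red |
| 24 | 57/81 = 70.4% | amber |

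With equal arms the measured rate would be two thirds of the true rate: 90% true adherence would read as 0.90 × 2/3 = 60%. With the exclusions confined to the single-route arms, the ceiling is 100% and 90% reads as 90%.

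**The case against.** The strongest reply is that nobody would program a set requiring both treatments and neither. The combined rule speaks of criteria for both interventions, which can be taken to mean course delivery; the closing sentence needs both routes; and section 7.1 defines the arm that way. This stands as to intent. It does not make the stated rule correct.

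The SAP may give the right definition, since section 14.2.4 leaves full details to it. But the protocol does not leave this definition open: it states it. A SAP that departed from it silently would put the two documents in conflict.

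On timing, the closing sentence is introduced as an additional requirement, so failing one of two joint conditions is not in itself a contradiction. That is fair. What remains is an ambiguity for a small group who start in the last days of the window; section 5.1 asks that treatment ideally start on the same or next working day after consent.

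A reader might also infer that the pilot adherence rate is bound to be red. The documents do not support that. Section 7.11.1 introduces its definitions for the per-protocol analysis, and section 8.1 speaks of adherence to the treatment allocation, under which a combined-arm participant who received both routes would ordinarily count as adherent. Nor is 67% a fixed ceiling: the minimisation has a random element, and 24 of 81 in the combined arm would give amber. Red leads to discussion with the Trial Steering Committee and funder, not an automatic stop.

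**Conclusion.** The combined-arm adherence rule contradicts itself. Applied exactly as written, it leaves 0 of 175 combined-arm participants in the per-protocol set and no per-protocol comparison of combination versus oral. This rests on the wording alone and needs no numerical assumption.

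The reach is limited. The affected analysis is secondary or sensitivity and covers the primary outcome only. The intention-to-treat analysis and the sample size do not depend on it. Because the intent can be recovered from the next sentence, the practical risk is an undocumented or late choice of who counts as per protocol, not an arm that would really be reported as empty.

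The 4-week mismatch is a secondary ambiguity confined to late starters; the protocol gives no basis for counting them. For the pilot, the supported statement is only that section 8.1 does not name its adherence definition. The figure of about 67% holds on two conditions that the protocol does not establish: literal carry-over of section 7.11.1 and roughly equal arms.

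**What to change.** - **Section 7.11.1, exclusions.** State that the two clauses excluding the other route apply only to the single-route arms, and that the combined arm must meet the course-delivery criteria of both interventions.
- **Section 7.11.1, timing.** Reconcile the inherited 4-week initiation limit with the closing sentence, which ties the 4 weeks to oral treatment and lets the injection fall up to four days either side, so that late starters are classified one way. Make clear which treatment the timing phrase in the intratympanic definition refers to. Which start date governs is for the sponsor to settle.
- **Section 8.1.** Name the definition behind the pilot adherence rate: the corrected arm-specific definitions or another stated one.

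The cost is a few sentences, matched in the SAP. Treatment, data collection and sample size need not change. The correction should be made before outcome data are seen, and the section 8.1 wording before the pilot adherence rate is calculated.
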